### Data Management and Analysis

Primary data are first entered in Epi Info software (version 7; Centers for Disease Control and Prevention). Data will be analyzed using both Epi Info 7 and SPSS software (version 23; IBM Corp). Mean OOP expenditure incurred due to the treatment modalities will be calculated. The OOP expenditure will be reported in Indian rupees. For international comparison, expenses will be converted to US dollars using an appropriate conversion rate. Indirect expenditure will be calculated for the duration of follow-up treatment using a human capital approach by assessing the wage loss of the caregivers [41]. Financial risk will be assessed in terms of catastrophic health expenditure and distress financing. An expenditure on DMD treatment that exceeds the threshold of 40% of nonfood household consumption expenditure is considered a catastrophic health care expenditure [42,43]. Households that had to either borrow money (with or without interest) or sold their assets (such as land, home, cattle, etc) to cope with DMD-related expenditure will be classified as having faced distress financing [38,44,45]. Multiple logistic regression analysis will be performed to examine the risk of catastrophic health expenditure and distress financing with covariates, including age, income status, treatment modality, education, locality, and stage at the time of diagnosis. Sensitivity analysis will be carried out to assess the prevalence of catastrophic expenditure at varying cutoff levels (ie, 20%-50%).

The HRQOL of the patients will be assessed by the EQ-5D-5L tool. This tool comprises the EQ-5D descriptive system and a visual analog scale (EQ VAS). The EQ-5D-5L descriptive system has 5 dimensions (ie, mobility, self-care, usual activities, pain or discomfort, and anxiety or depression). Each of these dimensions has a response in the form of 5 levels of perceived problems: no problems (level 1), slight problems (level 2), moderate problems (level 3), severe problems (level 4), and extreme problems (level 5). Thus, a unique health state is defined by combining 1 level from each of the 5 dimensions. The EQ VAS records the patient’s self-rated health on a VAS, where the end points are labeled as “The best health you can imagine” and “The worst health you can imagine.” The analysis of the QoL utility scores based on the EQ-5D-5L tool will be done as recommended in the user guide. Each of the patient’s condition or state at a particular time period will be referred to in terms of a 5-digit code. For example, state 11111 implies no problems on any of the 5 dimensions, while state 55555 indicates extreme discomfort in each of the dimensions. Each of these states are further converted into a single index utility value based on the recently generated tariff value set for the Indian population [46,47].

As mentioned earlier in this paper, the self-administered WHOQOL-BREF tool is used to assess the QoL of caregivers. This tool has 26 items describing 4 QoL domains, namely, physical health (7 items), psychological health (6 items), social relationships (3 items), and environmental health (8 items). It also contains items for general QoL and overall health (2 items). The response to each item is recorded in 5 levels and scored from 1 to 5. The raw scores will be converted into transformed scores ranging from 4 to 20. Later, these transformed scores will be converted into main domain scores ranging from 0 to 100, with higher scores indicating better QoL [48].

Correlations of HRQOL in children and QoL of caregivers in all 4 domains at the baseline will be assessed with socioeconomic status (SES), COI, and also with each other. Multiple linear regression analysis will be conducted to address the confounders (eg, age at baseline, family structure, type of disease, family history, family structure, education, and SES).

Economic burden and QOL data will be analyzed as per the study objective, and comparative analysis will be done to justify the hypothesis. Percentage, mean, and SD values will be recorded, and the chi-square test, paired *t* test, and Mann-Whitney *U* test will be carried out for statistical analysis. SPSS software (IBM Corp) will be used for the analyses.

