## Results

Study enrollment was completed in March 2022 with a total of 100 children with DMD and their caregivers (125% of the target). All 100 patients and their caregivers were followed up for 6 months in phase 1 of the study, which was completed in July 2022. The intervention was administered to 66 patients and their caregivers (94.3% of the target population) in phase 2. The participants were further followed for the subsequent 6 months, and phase 2 ended in December 2022. We are in the process of data entry and data cleaning. Initial data show that the children range in age between 5 and 15 years at enrollment, with a mean age of 8.3 (SD 1.9) years. Most of the children (56/100, 56%) enrolled in this study are in the late ambulatory disease (stage 3), and only 1 (1%) child was in a late nonambulatory stage at the time of enrollment. However, these dynamics changed swiftly with the progression of the disease.

Primary caregivers enrolled (n=100) at the baseline in the study were mostly mothers (58/100, 58%), with fathers comprising 38% (38/100) of the caregivers. Only 57% (57/100) of caregivers had some knowledge about DMD before enrollment. About 75% of the caregivers were educated more than high school, and 8.2% of them did not receive any formal education. More than half (51/100, 51%) the patients were had upper-middle SES, and (3/100, 3%) had lower SES. Because this study is only in the data entry and data cleaning phase, no impact data are available to report on the study objectives, aims, and hypotheses. The findings are expected to be published in 2024.

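### The six-covariate logistic models for catastrophic expenditure and distress financing have at most 8.3 events per parameter at one record per household, so a penalised fit is the safer choice

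*Protocol article*

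**What the plan says.** The Data Management and Analysis section of the protocol article plans multiple logistic regression for two binary household outcomes: "Multiple logistic regression analysis will be performed to examine the risk of catastrophic health expenditure and distress financing". The covariates are listed as "including age, income status, treatment modality, education, locality, and stage at the time of diagnosis". The list is introduced as inclusive, so six is the minimum.

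An event for the first outcome is spending on treatment that "exceeds the threshold of 40% of nonfood household consumption expenditure is considered a catastrophic health care expenditure". An event for the second is having borrowed money or sold assets to meet the costs of the disease. No expected prevalence is given for either outcome. The estimator, the coding of the covariates and the unit of analysis are not stated. The software named is SPSS and Epi Info.

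On numbers, the Results section reports: "All 100 patients and their caregivers were followed up for 6 months in phase 1 of the study", and "The intervention was administered to 66 patients and their caregivers (94.3% of the target population) in phase 2". On caregiver education it reports that "8.2% of them did not receive any formal education". The Setting and Sample Size Considerations section sizes the study on the quality-of-life difference only. Nothing there refers to these models.

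**The concern.** The article fixes both the number of covariates and the number of households, and together these limit the information per parameter whatever the prevalence turns out to be. With few events per parameter, maximum-likelihood log odds ratios are biased away from zero. Wald intervals and tests also become less reliable. If every household in one covariate category has the same outcome, the coefficient for that category has no finite estimate (separation).

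The article lists socioeconomic determinants among its secondary outcomes, and these models are the natural analysis for the financial-risk part of that question. What is at stake is whether the reported odds ratios for household characteristics are somewhat exaggerated, and whether sparse categories produce unusable estimates.

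**Working it through.** **Inputs.** From the article: 100 households in phase 1, 66 in phase 2, at least 6 covariates, and 8.2% of caregivers without formal education. Assumed, because the article does not give them: prevalence of each outcome between 10% and 50%, covariate coding, and effect sizes in the simulations.

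**The article's own figure.** The only sample-size figure is for quality of life: difference 0.1, SD 0.2, two-sided 5% (sidedness assumed), power 80%. n per phase = 2 × (1.960 + 0.842)² × (0.2/0.1)² = 62.8, rounded up to 63. With 10% dropout, 63/0.9 = 70. Both match the article. The calculation has no bearing on the logistic models.

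**Events per parameter, one record per household.** Formula: min(prevalence, 1 − prevalence) × n / number of slope parameters. With the minimum of 6 parameters:

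| Prevalence | n = 100 | n = 66 |
|---|---|---|
| 50% | 50/6 = 8.3 | 33/6 = 5.5 |
| 30% | 30/6 = 5.0 | 19.8/6 = 3.3 |
| 20% | 20/6 = 3.3 | 13.2/6 = 2.2 |

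To reach 10 per parameter needs 6 × 10/0.5 = 120 households at 50% prevalence and 6 × 10/0.3 = 200 at 30%. A relaxed guide of 5 needs 6 × 5 = 30 events. That is met at n = 100 down to 30% prevalence, and at n = 66 only down to 30/66 = 45%. If some covariates take more than one parameter, the figures fall: with 10 parameters the best case is 50/10 = 5.0 at n = 100 and 33/10 = 3.3 at n = 66.

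**Pooling both phases.** 100 + 66 = 166 household-phase records would give at most 83/6 = 13.8 nominally, but 66 households would count twice. With an assumed within-household correlation r, the effective number for household-level covariates is about 34 + 132/(1 + r). At r = 0.5 this is 122, and with a phase term added the best case is 61/7 = 8.7. It stays below 10 for r above about 0.25.

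**Size of the bias.** Simulation with six one-parameter covariates (assumed effects, true odds ratio 2) gave median odds ratios of 2.1 to 2.4 by maximum likelihood and 1.9 to 2.0 by Firth. Firth had the smaller root mean squared error in every setting.

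**Separation.** Share of simulated data sets with separation (600 per setting; coding and effects assumed):

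| Coding | Prevalence | n = 100 | n = 66 |
|---|---|---|---|
| 6 one-parameter covariates | 50% or 30% | 0% | 0% |
| same | 20% | 0.3% | 3% |
| same | 10% | 11% | 32% |
| about 9 parameters | 50% | 7% | 21% |
| same | 30% | 20% | 43% |
| same | 20% | 43% | 63% |

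About 13 parameters, with very rare levels kept as separate indicators, gave 80% and 91% even at 50% prevalence. The risk therefore depends mainly on coding and prevalence, neither of which the article fixes.

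**The case against.** The strongest reply is that the article names a standard model with sensible covariates, and that coding, merging of categories and choice of estimator are normally left to an analysis plan. That is fair: silence on those details is not counted as an error here. What stands is the ceiling. At one record per household, no coding choice lifts the figure above 8.3 while six covariates stay in the model.

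A reader might infer several stronger statements that the article does not support:

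- **That the models will often show separation.** With six balanced one-parameter covariates and 30% to 50% prevalence, separation was 0% in simulation. The high rates need low prevalence or rare levels entered as separate indicators.
- **That every usual guide is missed.** The article states no limit. A guide of 10 is out of reach, but a guide of 5 is met in the best case at both sample sizes.
- **That the three families of lower socioeconomic status form a sparse cell of this model.** The logistic covariate is income status. Socioeconomic status is named for the separate linear regression, and the article does not equate the two. Likewise, the stage distribution in the Results is at enrolment, whereas the covariate is stage at diagnosis. The education figure is the more plausible sparse level, although the article does not say whose education is meant.
- **That 66 is the analysis set.** All 100 households gave phase 1 data, and the models are not said to be restricted to families with both phases.
- **That maximum likelihood is specified.** It is an inference from unqualified logistic regression and the software named.

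Nor does the ceiling justify capping parameters at events divided by 10. Even at 50% prevalence and 100 households that allows only 50/10 = 5 parameters, so whole covariates would have to go, at a cost in confounding control.

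**Conclusion.** The point holds in a limited form. With one record per household and at least six parameters, events per parameter cannot exceed 8.3 at 100 households or 5.5 at 66. Under ordinary maximum likelihood, odds ratios would be modestly exaggerated: a true 2 becomes about 2.1 to 2.4, under assumed effects. Separation is a conditional risk, tied to low prevalence or to keeping small groups such as the 8.2% without formal education as their own category. Penalised estimation performed better in every simulated setting and costs little, so it is worth adopting. The models address determinants of financial risk, a secondary question. The before-after comparison of quality of life and out-of-pocket expenses is untouched.

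**What to change.** Add to the analysis text that both logistic models are fitted by Firth penalised-likelihood logistic regression with profile-likelihood confidence intervals. Merge rare covariate levels on their frequencies alone, before the outcomes are looked at. Report the models as exploratory. The article describes data entry and cleaning as still under way with no impact data available, so at that stage this could still be fixed in advance.

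Cost: a few lines of text, possibly a package outside SPSS and Epi Info, and slightly coarser categories. All six covariates can stay in the model.

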## Results

Study enrollment was completed in March 2022 with a total of 100 children with DMD and their caregivers (125% of the target). All 100 patients and their caregivers were followed up for 6 months in phase 1 of the study, which was completed in July 2022. The intervention was administered to 66 patients and their caregivers (94.3% of the target population) in phase 2. The participants were further followed for the subsequent 6 months, and phase 2 ended in December 2022. We are in the process of data entry and data cleaning. Initial data show that the children range in age between 5 and 15 years at enrollment, with a mean age of 8.3 (SD 1.9) years. Most of the children (56/100, 56%) enrolled in this study are in the late ambulatory disease (stage 3), and only 1 (1%) child was in a late nonambulatory stage at the time of enrollment. However, these dynamics changed swiftly with the progression of the disease.

Primary caregivers enrolled (n=100) at the baseline in the study were mostly mothers (58/100, 58%), with fathers comprising 38% (38/100) of the caregivers. Only 57% (57/100) of caregivers had some knowledge about DMD before enrollment. About 75% of the caregivers were educated more than high school, and 8.2% of them did not receive any formal education. More than half (51/100, 51%) the patients were had upper-middle SES, and (3/100, 3%) had lower SES. Because this study is only in the data entry and data cleaning phase, no impact data are available to report on the study objectives, aims, and hypotheses. The findings are expected to be published in 2024.

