**Results:**

Participant recruitment began in July 2021. The study is ongoing and expected to be completed by March 2023. The findings based on baseline data are expected to be submitted for publication in 2023.

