### Data Collection

At the time of recruitment, primary caregivers are interviewed on their social and demographic characteristics and QoL. Further, after the initiation of phase 1, these caregivers are contacted again prospectively to assess the economic burdens they face by collecting data on out-of-pocket (OOP) expenses incurred during the treatment of DMD. The data on economic burden include information on household consumption expenditure, patient-level expenses incurred on diagnosis and treatment related to DMD, and coping mechanisms for dealing with DMD. A pretested semistructured schedule, adapted from previous studies in similar settings, is used to interview the patients [37-39]. Cost-of-illness (COI) analysis is carried out to assess OOP expenses, which are further classified as direct and indirect expenses [40]. Expenditure on the diagnosis, drugs or consumables, hospitalization, user fee, or procedure fee is considered direct health care expenditure. Transportation, boarding, loading, and food are taken as direct non–health care expenditures. Wage or income loss by the accompanying caregivers during the period of treatment is considered an indirect expenditure.

Information on economic burden is gathered from the caregivers throughout the follow-up period of 12 months. Data are collected during their physical visits as well as telephonically every month.

HRQOL of the patients and their caregivers are gathered at the baseline and then at the completion of phases 1 and 2. QoL of caregivers is also recorded at the 3 data points (baseline, end of phase 1, and end of phase 2). The study design is further explained in Figure 1.

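### The reported dates cannot hold six months of phase 1 for all 100 children, nor 6 + 6 months for anyone enrolled after 31 December 2021

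*Protocol article*

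**What the plan says.** Under Study Design, the protocol article sets follow-up per patient. Routine care is observed for six months from recruitment. Phase 2 then starts when that patient has finished phase 1, and lasts a further six months. Data Collection adds that cost information is gathered "throughout the follow-up period of 12 months".

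The calendar dates are in two places:

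- Abstract, Results: "Participant recruitment began in July 2021", and the study is "expected to be completed by March 2023".
- Main Results section: "Study enrollment was completed in March 2022 with a total of 100 children with DMD and their caregivers". It continues: "All 100 patients and their caregivers were followed up for 6 months in phase 1 of the study, which was completed in July 2022". On phase 2 it says: "The intervention was administered to 66 patients and their caregivers (94.3% of the target population) in phase 2". Those participants are said to have had six more months, and "phase 2 ended in December 2022".

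The list of study outcomes labels the QoL comparison as phase 1 (0-6 months) against phase 2 (7-12 months). The out-of-pocket (OOP) measure is a mean with and without the intervention, and no time unit is given.

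**The concern.** The last enrolment month and the end of phase 1 are only four calendar months apart, yet every child is said to have had six months of phase 1. The last enrolment month and the end of phase 2 are nine calendar months apart, against a planned twelve.

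This matters because length of follow-up defines the two conditions being compared. There is no concurrent control, so each child's own phase 1 is the reference for phase 2. A cost that accumulates over time depends on how many months were observed. The article gives no time unit for mean OOP, and Data Management and Analysis computes indirect expenditure over the duration of follow-up, a quantity that grows with months observed. If some windows were shortened and phase totals were compared, part of any cost difference would reflect observation time. The direction would depend on which phase was cut. QoL is measured at time points and does not accumulate, but the nominal 6- and 12-month assessments would fall earlier than labelled.

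**Working it through.** **Inputs.** Recruitment began July 2021 (Abstract, Results). Enrolment ended March 2022, phase 1 was completed July 2022 and phase 2 ended December 2022 (Results). Each phase lasts six months per child, twelve in all (Study Design; Data Collection). No days of the month are given, so both extremes are shown. One month is taken as 30.4375 days.

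**Can the stated six months be reproduced?** For early enrollees, yes. A child enrolled on 1 July 2021 finishes phase 1 on 1 January 2022 and phase 2 on 1 July 2022, well inside the stated ends. For all 100, no:

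- Latest enrolment for six months by 31 July 2022: 31 July 2022 − 6 months = 31 January 2022.
- Latest enrolment for twelve months by 31 December 2022: 31 December 2022 − 12 months = 31 December 2021.
- A March 2022 enrollee on the planned schedule: + 6 months = September 2022; + 12 months = March 2023.

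**Time available to a March 2022 enrollee on the stated dates**

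| Interval | Most generous days | Least generous days | Planned |
|---|---|---|---|
| Phase 1, to July 2022 | 1 Mar to 31 Jul: 152 days / 30.4375 = 5.0 months | 31 Mar to 1 Jul: 92 days = 3.0 months | 6 |
| Both phases, to December 2022 | 1 Mar to 31 Dec: 305 days = 10.0 months | 31 Mar to 1 Dec: 245 days = 8.0 months | 12 |

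The shortfall is therefore 1 to 3 months in phase 1 and 2 to 4 months overall.

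**Phase 2 for a child who finishes phase 1 in July 2022.** From 1 July to 31 December is 183 days (6.0 months). From 31 July to 1 December is 123 days (4.0 months). So a phase 2 that starts in July may be complete, or up to 2/6 (33%) short.

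**How many children could be involved?** Enrolment dates by child are not given. Assuming even accrual over the nine months from July 2021 to March 2022:

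- February and March: 2/9 = 22% could not have six months of phase 1 by the end of July.
- January to March: 3/9 = 33% could not have twelve months by the end of December.
- July to December: 6/9 = 67%, about 67 of 100, could have had both phases in full.

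These shares are illustrative and change with the true accrual pattern.

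**The case against.** A reader might infer that the phase windows were unequal and that costs by phase are therefore not comparable. The documents do not support that, for four reasons.

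1. **A date may simply be wrong.** The design sections agree with one another, and the conflict lies in a status report. The March 2023 completion in the Abstract is exactly March 2022 plus twelve months. It is only a forecast, so it does not settle the matter. The same paragraph of Results has another loose figure: 100 children as 125% of target implies a target of 80 (100/1.25), while 66 as 94.3% implies 70 (66/0.943). A reporting slip is plausible.
2. **Only 66 of 100 received the intervention.** Under even accrual about 67 children enrolled by December 2021, so the treated group could consist entirely of children with 6 + 6 full months. The article does not say so, and it does not explain why 34 were not treated, so this is possible but not shown.
3. **Short need not mean unequal.** A child enrolled on 1 March 2022 could have 152 days to 31 July and another 152 days from 1 August to 31 December, about five months each.
4. **No section says that phase totals are compared.** Costs are collected monthly, so a per-month mean is available. The 40% rule for catastrophic expenditure is a ratio, distorted only if its two parts cover different windows.

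A reader might also infer that phase 2 cost could be understated by half. That needs a three-month phase 2, hence a phase 1 running to the end of September 2022, which contradicts the stated July end.

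All of this stands against a claim of bias. None of it rescues the statement that all 100 had six months of phase 1 by July 2022 with enrolment into March. That conflict does not depend on which 66 were treated.

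**Conclusion.** The calendar conflict is certain on the dates as printed. Six months of phase 1 for all 100 children is impossible if any enrolled after 31 January 2022, and the article says that enrolment ran to March. Full 6 + 6 follow-up is impossible for anyone enrolled after 31 December 2021 if phase 2 ended in December 2022. For a March 2022 enrollee the available time is 3 to 5 months of phase 1 and 8 to 10 months in all. This rests only on the stated months and on follow-up being counted from each child's recruitment, as Study Design says.

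Whether any follow-up was actually shortened, and whether any of the 66 treated children were affected, cannot be told from the article. The 22% and 33% shares hold only under assumed even accrual. The point is worth correcting because follow-up length defines the phases, mean OOP has no stated time unit, and the safeguard costs very little.

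**What to change.** - Check the enrolment, phase 1 and phase 2 dates against the enrolment log. Correct whichever is wrong, including the statement of six months for all 100 and the completion date in the Abstract.
- Report observed months per child in each phase, for all 100 and separately for the 66 treated.
- Define the OOP comparison as cost per observed month, within children who have both phases.
- For the 40% rule, take DMD spending and household consumption over the same window.
- If the log shows any shortened windows, repeat the primary comparison in children with a full 6 + 6 months.

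The cost is negligible. The dates should already be in the enrolment log, costs are collected monthly, and Results says the data are still being entered and cleaned. If the log shows that only a date was misprinted, correcting the text and stating the cost per month are enough.
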